### Conduct of the study

Figures 1 and 2 show, respectively, a flowchart of the study setup and the Standard Protocol Items: Recommendations for Interventional Trials (SPIRIT) template. See Additional file 1 for the SPIRIT checklist.

**Fig. 1 Fig1:**
[figure not shown]
Flowchart of the study setup

**Fig. 2 Fig2:**
[figure not shown]
Example template of recommended content for the schedule of enrollment, interventions, and assessments

#### Presurgical period

After surgical consultation, the patients will receive written information about the study. Time will be devoted to responding to the patient’s questions before collecting the patient’s consent during the pre-anesthesia visit, which is used to confirm that the patient meets the inclusion criteria. If he/she agrees to participate in the research, this consultation will be immediately followed by a specialized consultation with a neuropsychologist trained to perform an assessment of functional decline and frailty in addition to a cognitive assessment. This visit is designed based on the experience of the epidemiology and geriatric units. The number of items in the questionnaire is limited to avoid fatigue in the participants, especially since the visit includes a measure of physical performance.

#### Randomization

On day 0, upon arrival at the operating room, centralized randomization on a website will be performed with stratification of the frailty status prior to surgery (phenotypic Fried scale in three categories: robust, pre-frail, frail) crossed with two categories of surgical risk: minor or major. This randomization will determine the modality of total intravenous anesthesia (manual or automated group). For the first arm, total intravenous anesthesia is achieved under the exclusive direction of an anesthesiologist with a BIS value maintained in the range 40–60 as the target — *the manual group* (this is the usual technique used for intravenous drugs). The BIS is an absolute value from 0 to 100 derived from the frontal EEG: 100 corresponding to a fully awake patient and 0 to a flat EEG. The second arm involves completely automated delivery; a proportional-integrative-differential (PID) algorithm is used to manage the administration of both propofol and remifentanil through a controller to reach a BIS target in the range 40–60 — *the automated group*. The PID algorithm means that the controller calculates the difference between the measured output and the setpoint (BIS = 50) to adjust the input value. The algorithm considers the present (proportional), past (integral), and future (derivative) error to adjust for the correction. At any moment, the automatic control can be over-ridden by the physician. This event is recorded for further analysis.

#### Anesthesia management

For anesthesia management, typical monitoring (electrocardiogram (EKG), pulse oximetry, noninvasive blood pressure) or invasive monitoring (neuromuscular blockade, capnography, inspiratory oxygen fraction) will be set up for the patient with mandatory BIS monitoring. Intubation or the establishment of a supraglottic device will be at the discretion of the anesthesiologist, as well as the use and selection of a muscle relaxant. Fluid management and hemodynamic control are left to the practitioner’s appreciation. Any perioperative events such as prolonged arterial hypotension, sudden bleeding, and myocardial ischemia may indirectly impair the patient's prognosis. Therefore, to limit any bias in the analysis, some targets were common among the investigators: limit any episode of arterial hypotension (meaning a drop >20% compared to baseline), avoid anemia (maintain hemoglobin >8 g/dl in absence of ischemic event), perform ST-segment monitoring, etc. All events are systematically recorded during anesthesia [12]*.* Prophylaxis against postoperative nausea and vomiting is administered according to the Apfel score [13]. Rapid tube removal after stopping anesthesia is strongly recommended to avoid any prolonged sedation in this cohort of patients. The investigator is not blinded to the anesthesia technique (control or automated), but he does not know the frailty status; likewise, the controller in the automated group does not know it. The patient and the neuropsychologist performing the postoperative assessment are blinded, and this decreases the risk of bias.

#### Follow-up

Postoperative care will follow the rules of standard care with an additional interview conducted between days 1–3 to ensure the absence of any complications and awareness. Leclerc [14] has previously described the questionnaire used to assess explicit memory. During the third month, a healthcare professional will telephone to determine the patient’s condition upon returning home (e.g., delayed complications, delirium, and need for a transitional care unit) and will seek to determine if any limitations in activity exist or, at the worst, if the patient has died. Finally, during the sixth month, a new specialized consultation will be planned with the repeated application of psychometric tests blinded to the mode of anesthesia used. The study ends with this consultation. If the patient refuses or is unable to come to the second visit, a telephone interview will be planned to assess his/her health, functional, frailty, and cognitive status. Regarding health and functional abilities, the same questions as those included in the questionnaire will be asked during the telephone interview. Cognitive functions will be examined using the screening tools that were validated by telephone: the F-TICSm questionnaire (French adaptation of a version of the phone MMSE) and the Category Fluency by Telephone (CFT) [15]. Frailty will be assessed by asking the participants about unintentional weight loss, fatigue, and physical activity. The measure of muscle weakness and slow walking speed will be approximated by any difficulties lifting a 5-kg bag and difficulties climbing up and down stairs.

Likewise, the following events will be documented: any event occurring between neuropsychological assessment (inclusion visit) and surgery (randomization) that is considered important by the physician anesthesiologist managing the patient and that may change the status of the patient and may lead to the patient being excluded from the study or declared as an undesirable effect in case of return to hospital, or any other surgery or medical event during this interval, or death.

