Slow walking. This is measured by determining the time it takes for a patient to walk 4 meters (threshold according to gender and height). Specifically, 1 point is given to any patient with a slow walk.Muscle weakness. This is assessed by evaluating hand grip strength (threshold according to gender and body mass imdex (BMI)). Specifically, 1 point is given if the patient scores below the reference.

At the end of this assessment, a subject is classified as "frail" if the total criteria total more than 3. Subjects with a criterion of 1 or 2 are referred to as "pre-frail," and subjects with no criteria are considered "robust."

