### Statistical analysis

The main outcome will be defined as "the percentage of patients alive without loss of autonomy in the sixth month (26 ± 2 weeks) following surgery." By definition, death will be included as a permanent loss of autonomy of the subject. Secondary outcomes include a comparison of the postoperative complications using Dindo and Clavien's classification, a change in the Frail status (subclassified as robust, pre-frail, and frail) after 6 months according to Fried's scale, and the quality of anesthesia assessed through the total duration in the expected interval of BIS value (40–60), the total duration in too deep anesthesia (defined as a BIS value <40), and the occurrence of a suppression ratio. The period of analysis is only that during general anesthesia. Based on the published data, it is estimated that at 6 months, the mortality in this population will be approximately 8%, institutionalization will be required in one in five of the remaining cases, and in the patients who remain alive without institutionalization, a decline in ADL will occur in one subject in six in 6 months. This leads to an overall proportion of patients who will die or whose level of functioning will deteriorate after a scheduled major surgical intervention of 39.4%. We hypothesize that better control of the depth of anesthesia should reduce this figure by one third. Under these conditions, a sample of 430 patients, equally divided between the two anesthesia groups, leads to a Fisher’s exact test with a risk of first species bilateral of 0.05 to a power of 0.8 to highlight the expected difference, if it exists.

This research will include a randomization of 1:1 between the groups with stratification based upon the frailty status of the subject prior to the surgery, as determined using the phenotypic Fried scale in three categories (robust, pre-frail, and frail) crossed with two surgical risks (minor or major) [19] (Table 1). The randomization list with balancing groups is performed using a computer program; allocation to a group is performed automatically.

**Table 1 Tab1:** Determination of surgical risk (minor or major) in the elderly. (Adapted from Eagle [19])

Usual classification	Type of surgery	Adapted classification in elderly patients
Low Risk	Wall surgery without opening the peritoneal cavity	Low Risk
	Abscess drainage	
	Endoscopies	
	Proctology	
	Plastic surgery	
	Ophthalmic surgery	
Intermediate Risk	Intraperitoneal surgery	Major Risk

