The main limitation to our approach is the use of anesthesia in both groups using the BIS sensor, which is available at any moment for both groups. This could also lead to the optimization of the control group compared to the standard group. However, in the case of special morbidity as in elderly patients, this was the only way to make this comparison. Secondly, volatile anesthetics are not used in this study and may induce a different response. Thirdly, we have no knowledge of the rate of frail patients in the operating room, as surgeons can spontaneously reject an operation when faced with a patient with several comorbidities.

If our hypothesis is true, automated anesthesia could be recommended to maintain a similar frailty status among the elderly.

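### Six-month change in frailty status (a secondary outcome) switches from measured grip and gait to telephone self-report for patients who do not attend, so their change is partly a change of instrument

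*Protocol article*

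**What the plan says.** Under Frailty status, the protocol article builds the baseline class from five criteria. Exhaustion, physical activity and weight loss are obtained by questions. Slow walking and muscle weakness are measured. On walking it says: "This is measured by determining the time it takes for a patient to walk 4 meters", judged against a threshold for gender and height. Weakness is measured by hand grip, judged against a threshold for gender and BMI. No criterion present means robust; one or two means pre-frail.

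Under Follow-up, the month-6 visit repeats the assessment in person, with a fallback: "If the patient refuses or is unable to come to the second visit, a telephone interview will be planned". In that interview the three questioned criteria are asked again, but for the two measured ones the article says: "The measure of muscle weakness and slow walking speed will be approximated by any difficulties lifting a 5-kg bag", and the same sentence adds difficulty with stairs.

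Under Statistical analysis, one secondary outcome is "a change in the Frail status (subclassified as robust, pre-frail, and frail) after 6 months". The Discussion adds that the cohort may inform on how frailty evolves after surgery, and closes by saying that, if the hypothesis is true, "automated anesthesia could be recommended to maintain a similar frailty status among the elderly".

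**The concern.** A change score or class transition is interpretable when both ends are measured in the same way. For telephone patients they are not. The baseline end uses a stopwatch and a dynamometer with individual thresholds. The month-6 end uses two yes/no self-reports with no thresholds, about tasks (lifting a bag, climbing stairs) that differ from those measured.

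The Follow-up section treats the other domains differently. Functional abilities are covered by the same questions as in the visit questionnaire, and the cognitive telephone tools are described as validated for that use. No such statement is made for the two frailty substitutes.

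Two uses of the data are at stake. The first is the within-patient description of the course of frailty, where spurious transitions count directly as change. The second is the comparison of arms on this secondary outcome, where they act as misclassification. The telephone route is open to those unable to attend as well as those who decline, so the affected patients may well be in poorer health than the rest.

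**Working it through.** **Is there a plan figure to reproduce?** Not for this outcome. The only computed figure is the sample size of 430, which belongs to the primary outcome. It reproduces: the event rates are 39.4% and 39.4% × 2/3 = 26.3%, and full enumeration of the two-sided Fisher's exact test at 215 per arm gives power 0.802. It has no bearing on the frailty outcome.

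**Which criteria change instrument (Frailty status against Follow-up)**

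| Criterion | Inclusion | Month 6 by telephone |
|---|---|---|
| Exhaustion | question | question |
| Physical activity | questionnaire | question |
| Weight loss | question | question |
| Slow walking | timed 4 m walk, threshold | difficulty with stairs |
| Muscle weakness | grip strength, threshold | difficulty lifting 5 kg |

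Two of the five criteria switch.

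**How far one false positive moves a patient.** By the class definitions:
- Robust (0 criteria) plus one false positive gives 1, which is pre-frail. The class changes.
- Pre-frail with 1 plus one gives 2, which is still pre-frail.
- Pre-frail with 2 plus one gives 3. Frail is defined as more than 3, so as written this patient does not become frail (a score of exactly 3 is left without a class).

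For spurious worsening from a single item, the clear case is therefore robust to pre-frail. The opposite error is also possible: a patient who is pre-frail on measured grip alone and reports no difficulty with the bag would appear to have become robust.

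**Size among unchanged robust telephone patients.** Let f be the chance that an item is positive when the measured criterion would be negative. The documents do not give f. Assume 5%, 10% or 20%, with the two items independent. The chance of at least one false positive is 1 − (1 − f)²:
- f = 0.05: 1 − 0.95² = 9.8%
- f = 0.10: 1 − 0.90² = 19.0%
- f = 0.20: 1 − 0.80² = 36.0%

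**Size among all unchanged robust survivors.** Multiply by the telephone share, which is also not given. Assuming 5% to 30%, the range runs from 0.05 × 0.0975 = 0.5% to 0.30 × 0.36 = 10.8%. For context on attendance, the Statistical analysis section expects 8% mortality, leaving 430 × 0.92 = about 396 survivors, and institutionalization in one in five of them, about 79.

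**Effect on the arm comparison.** With equal item error in both arms, the spurious difference among unchanged robust patients is (difference in telephone share) × [1 − (1 − f)²]:
- Equal shares: 0 for every f.
- 10% against 20% (assumption): 0.10 × 0.0975, 0.10 × 0.19 and 0.10 × 0.36, which is 1.0, 1.9 and 3.6 percentage points.

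**The case against.** The strongest reply is that the fallback is an openly stated approximation that limits missing data, that it touches two of five criteria in a secondary outcome, and that handling assessment mode is ordinary analysis-plan work. Much of this stands. The primary outcome is protected: the functional questions are the same by telephone, and death counts there as loss of autonomy. Patient and month-6 assessor are blinded, so with equal telephone use and equal item error in both arms the switch adds noise to the randomized comparison and does not bias it. Telephone patients also include those who simply decline to come.

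What does not stand is that an analysis plan alone can repair it. It can separate or exclude telephone patients, but it cannot build a like-for-like change for them from items never asked at inclusion. The full questionnaire, which is not shown, might contain the two items; the article does not list them.

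A further objection is that computing change on self-report for some patients and on measurements for others still pools two instruments. That is fair. Like-for-like change within each patient removes the spurious transitions caused by switching, but not the difference between forms, which is why an agreement check and an in-person-only analysis are needed as well.

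A reader might also infer that deaths drop out of the frailty outcome and leave a survivors-only comparison, because its three classes are all living states. The article does not say so. It is silent on deaths for this outcome, and a rule for them is commonly set in the analysis plan. Ranking death as the worst category is one option among several.

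**Conclusion.** The point holds for the secondary outcome of change in frailty status. For patients assessed by telephone at month 6, change combines true change with the switch from measured to self-reported grip and gait. Under assumed independent false-positive rates of 5% to 20% per item, 9.8% to 36% of truly unchanged robust telephone patients would be recorded as having become pre-frail. Neither the telephone share nor the accuracy of the items is in the documents, so these are illustrations of scale and not estimates.

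The consequence is a distorted description of the course of frailty and added misclassification in the arm comparison. It would be tempting to call the arm comparison biased, but the documents do not support that: bias requires telephone use or item error to differ by arm, which is possible if the treatment affects health but is not established. Nor does it follow that the closing recommendation rests on this outcome alone. That sentence is conditional on the trial's hypothesis, which the Discussion frames as fewer patients with severe impairment of autonomy and the Background frames as mortality and frailty together. The primary outcome is untouched.

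**What to change.** 1. Ask the 5-kg bag and stairs questions of every patient at inclusion and again at month 6, whichever way month 6 is conducted.
2. Record the mode of the month-6 assessment (in person or telephone).
3. For telephone patients, compute change on the self-report form at both times. Keep the measured Fried class for stratification and covariate adjustment, so that the baseline class used there stays the one used at randomization.
4. Use patients who have both the measurements and the two items to report agreement between the forms.
5. Add a sensitivity analysis restricted to patients assessed in person at month 6.

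The cost is two short questions per visit and some analysis wording. Patients already included lack the baseline items, so like-for-like self-report change cannot be computed for them. They can still contribute through the measured form if they attend in person, and to the agreement check if their month-6 visit lies ahead. The Trial status section reports the first 50 patients included; if that is still about the position, 430 − 50 = 380 could be asked from inclusion. The gain shrinks as recruitment proceeds, so the change should be made early.

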### Data collected

#### Demographic data

Typical demographic data, such as age, sex, BMI, and ASA status, will be collected. Comorbidity using the Charlson index will be recorded to correlate with the follow-up results. Finally, a specific investigation regarding surgery or a fall during the previous year will be performed. This section also includes a global health assessment to detect any symptoms of depression and any signs of social isolation.

#### Functional abilities

Any limitations in activity will be evaluated using the six activities of daily living (ADL) included in the Katz index [16, 17], which consist of eating, bathing, dressing, toileting, transferring (walking), and continence, as well as instrumental activities of daily living (IADL) [18], such as food preparation, the ability to use a telephone, housekeeping, shopping, and the ability to manage one’s finances.

#### Cognition

Cognitive function will be assessed using different tests. First, the MMSE will be used to confirm the absence of severe cognitive impairment with a score above 15. Nevertheless, if the patient remains self-sufficient, this is not an exclusion criterion. Then additional tests, such as the Trail Making Test, word recall, verbal fluency, and drawing a clock at 10:10, are performed.

#### Frailty

Frailty as a phenotype was calculated using Fried's assessment as previously described. However, Edmonton's criteria will also be collected because they explore other dimensions such as social aspects or the patient's medication. Finally, the Timed Up and Go test was added to explore proprioceptive dimensions.

#### Collection of data

During every visit, a case report form (CRF) — created after the written consent is obtained — with an anonymous number is filled out by any investigator involved (doctor, neuropsychologist) from the inclusion to the last interview with the neuropsychologist at the sixth month. In case of a major undesirable event, the number can be unmasked to inform or find the patient if any residual risk exists. The data monitoring in this study will be locally managed without any sponsor by our clinical research team (DRCI Hôpital Foch, URC Besançon), and the final validation will be performed by a specialized society with no competing interest in this study. There are no financial or other competing interests for principal investigators for the overall trial and each study site. The study is supported only by a grant from the French Health Ministry.

### Statistical analysis

The main outcome will be defined as "the percentage of patients alive without loss of autonomy in the sixth month (26 ± 2 weeks) following surgery." By definition, death will be included as a permanent loss of autonomy of the subject. Secondary outcomes include a comparison of the postoperative complications using Dindo and Clavien's classification, a change in the Frail status (subclassified as robust, pre-frail, and frail) after 6 months according to Fried's scale, and the quality of anesthesia assessed through the total duration in the expected interval of BIS value (40–60), the total duration in too deep anesthesia (defined as a BIS value <40), and the occurrence of a suppression ratio. The period of analysis is only that during general anesthesia. Based on the published data, it is estimated that at 6 months, the mortality in this population will be approximately 8%, institutionalization will be required in one in five of the remaining cases, and in the patients who remain alive without institutionalization, a decline in ADL will occur in one subject in six in 6 months. This leads to an overall proportion of patients who will die or whose level of functioning will deteriorate after a scheduled major surgical intervention of 39.4%. We hypothesize that better control of the depth of anesthesia should reduce this figure by one third. Under these conditions, a sample of 430 patients, equally divided between the two anesthesia groups, leads to a Fisher’s exact test with a risk of first species bilateral of 0.05 to a power of 0.8 to highlight the expected difference, if it exists.

This research will include a randomization of 1:1 between the groups with stratification based upon the frailty status of the subject prior to the surgery, as determined using the phenotypic Fried scale in three categories (robust, pre-frail, and frail) crossed with two surgical risks (minor or major) [19] (Table 1). The randomization list with balancing groups is performed using a computer program; allocation to a group is performed automatically.

**Table 1 Tab1:** Determination of surgical risk (minor or major) in the elderly. (Adapted from Eagle [19])

Usual classification	Type of surgery	Adapted classification in elderly patients
Low Risk	Wall surgery without opening the peritoneal cavity	Low Risk
	Abscess drainage	
	Endoscopies	
	Proctology	
	Plastic surgery	
	Ophthalmic surgery	
Intermediate Risk	Intraperitoneal surgery	Major Risk
	Laparoscopic surgery	
	Endarterectomy	
	Ear, nose and throat (ENT) surgery	
	Prostate surgery	
	Orthopedic surgery	
	*Intermediate risk in elderly (>70 years old)*	
Major Risk	Intermediate surgery performed in emergency	
	Unstable hemodynamic conditions	
	Vascular surgery (aortic and peripheral) and thoracic surgery	
	Prolonged surgery (>4 h) with high fluid displacement or major bleeding	

A statistical intention-to-treat analysis will compare both groups (manual and automated general anesthesia) after 6 months through the generalized linear mixed model (GLIMM), which considers the type of anesthesia, frailty status, and surgery. A significant threshold at 0.05 is defined, and the software used for the analysis will be either R3.0 or SPSS20. A logistic regression or a multivariable analysis could be performed to establish some predictive factors if relevant. To ensure that the hypothesis was correct compared to observed data, an intermediary analysis is planned after 100 inclusions.

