## Background

In 2010, 16.7% of the French population was over the age of 65, with that number projected to rise to 20% in 2020 according to the National Institute of Statistics and Economic Studies (INSEE). Indeed, this trend is of concern in every developed country. Moreover, progress in surgical techniques and control of anesthesia means that surgical procedures are becoming more common in the elderly, with approximately 30% of surgeries conducted in patients over the age of 70, according to the latest epidemiological surveys. However, aging is accompanied by certain physiological changes that may have a critical impact on the patient’s postoperative outcome, including reduced adaptation in cardiac output to stress, reduced lung compliance, decreased cerebral blood flow, thermal dysregulation, loss of functional units in the kidneys, and decrease in renal blood flow [1].

Increasing age in the general population has led to the development of the concept of frailty to better assess the geriatric patient population [2]. Frailty represents a decrease in homeostasis and resistance to stress, and it increases the vulnerability of a person exposed to the risk of unfavorable changes (morbidity or death) disproportionately in relation to the event [2, 3]. Physiologically, fragility results from the simultaneous impairment or decrease in physiological reserve in multiple systems. The early detection of at-risk individuals is accomplished through geriatric assessments using psychometric scales and the Fried score, which is the most widely used metric scale for frailty and includes five criteria for determining anesthetic or surgical perioperative risk factors. This type of assessment attempts to prevent functional decline and high morbidity and mortality in elderly surgical patients [4, 5]. In this specific situation, a relationship between depth of anesthesia and impaired postoperative outcome has been described in a large but retrospective cohort. This suggested a more pronounced impact on the elderly and especially in pre-frail or frail patients.

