### Frailty status

Although it does not appear systematically during aging, which suggests a genetic component and a role for environmental factors [8], the prevalence of frailty increases with age and ranges from 4% in subjects aged 65–69 years to 26% in subjects older than 85 years. Collard et al. estimated that frailty concerns 10% of people over the age of 65 [9]. Although the concept of frailty is now recognized, there is no consensual definition or screening tool for frailty. Instead, frailty is observed as an accumulation of deficits [10] or as an independent phenotype [4]. In both operational approaches, frailty is defined by the risk of death, functional disability, or institutionalization. Central to this model is the occurrence of sarcopenia, or muscle loss related to age, which is often caused by undernutrition. In this study, we have chosen the model of the frailty phenotype (Fried's scale) resulting from the US Cardiovascular Health Study (CHS), which describes the five operational criteria of frailty. To date, this scale is the most common assessment used in the literature because it allows a quick assessment of an elderly patient by any healthcare provider. The scale is based on the following assessments:Exhaustion. Exhaustion is classified using the Center for Epidemiologic Studies Depression Scale (CES-D) indicator: *I felt that everything I did was an effort; and I could not get going* with the following question: *How often in the last week did you feel this way?* The responses are rated as 0/rarely or none of the time (1 day), 1/some or a little of the time (1–2 days), 2/a moderate amount of the time (3–4 days), or 3/most of the time. Specifically, 1 point is given for subjects answering “2” or “3” to either of these questions.Resistance or aerobic activity (level of physical activity). The quantitative assessment of the energetic expense is performed by using the International Physical Activity Questionnaire-Elderly (IPAQ-E), which distinguishes three levels of activity (low, moderate, and high) according to time spent walking and performing moderate (e.g., carrying light loads, leisurely bicycle rides, or tennis) and vigorous activity (e.g., carrying heavy loads, digging, lifting a pack of six bottles, or speed bicycling) during the past 7 days [11]. Specifically, 1 point is given for low levels of activity.Unintentional loss of weight. Specifically, 1 point is given for a positive response to the question: *Have you lost more than 5 kg in the past year?*

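### The secondary frailty outcome records change between three categories although a 0–5 Fried count is available at both visits, so patients frail at baseline cannot be recorded as worsening and sensitivity is lost

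*Protocol article*

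**What the plan says.** The section Frailty status adopts the phenotype model that "describes the five operational criteria of frailty" and gives one point for each criterion, so every patient has a count from 0 to 5. It then groups the count. Robust means no criterion. "Subjects with a criterion of 1 or 2 are referred to as" pre-frail. A patient is frail "if the total criteria total more than 3".

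The section Follow-up plans a further specialized visit in the sixth month. Patients who cannot or will not attend have a telephone interview covering all five items, with grip strength and walking speed replaced by questions about lifting a bag and using stairs.

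The section Statistical analysis lists among the secondary outcomes "a change in the Frail status (subclassified as robust, pre-frail, and frail) after 6 months according to Fried's scale". It names no test, expected change or power for this outcome. Frail patients are eligible and form a randomization stratum (Randomization; Statistical analysis).

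Two other places bear on the choice. The Background says of the link between anesthetic depth and outcome: "This suggested a more pronounced impact on the elderly and especially in pre-frail or frail patients". The Discussion says that, if the hypothesis is true, "automated anesthesia could be recommended to maintain a similar frailty status among the elderly".

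**The concern.** The outcome is coarser than the data behind it. A pre-frail patient who goes from 1 to 2 criteria is recorded as unchanged. A frail patient who declines further is also recorded as unchanged, because no worse category exists. These are the groups in which the Background expects the larger impact.

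Two things are at stake. A real difference between arms on this outcome is more easily missed. And an observation of unchanged status is partly produced by the scale, so it supports the Discussion's recommendation less well than it appears to.

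**Working it through.** **The plan's own figure.** The only sample size in the article belongs to the primary outcome. With 39.4% in the manual arm and a one-third reduction, 0.394 × 2/3 = 0.263. The two-proportion formula at two-sided 0.05 and power 0.80 gives 400 in total, or 430 with continuity correction. Exact Fisher power at 215 per arm is 0.802. The 430 reproduces and does not depend on the frailty outcome.

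**What follows without any assumption.** Frail is the highest of three ordered categories, so no patient who starts there can move to a worse one.

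**Which steps are invisible, taking frail as 3 or more:**

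| Step in count | Category | Seen? |
|---|---|---|
| 0–1 | robust to pre-frail | yes |
| 1–2 | pre-frail throughout | no |
| 2–3 | pre-frail to frail | yes |
| 3–4 | frail throughout | no |
| 4–5 | frail throughout | no |

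Three of the five possible steps are lost. Read literally, the article puts frail above 3 and pre-frail at 1 or 2, so a count of 3 has no category and change is undefined for anyone at 3 at either visit.

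**Share of changes lost (assumed case mix).** The article gives no distribution of the count, and the Discussion says the rate of frail surgical patients is unknown. Let P(k) be the proportion with k criteria at baseline. The invisible share of one-step worsening is [P(1)+P(3)+P(4)] / [1−P(5)], and of one-step improvement [P(2)+P(4)+P(5)] / [1−P(0)]. For five assumed mixes (robust/pre-frail/frail, %), the invisible share over both directions is:

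- 60/33/7: 30%
- 50/40/10: 35%
- 40/47/13: 40%
- 25/50/25: 48%
- 15/45/40: 54%

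For worsening alone, the range is 29–60%. If a count of 3 were placed in pre-frail instead, it would be about 35–61%. A separate simulation (A, below) found 28–41% of all count changes invisible.

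**Power lost, same model on both scales.** Both simulations cover survivors only.

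*Simulation A.* Inputs: 390 patients assessed (430 × 0.92 = 395.6, less a few losses); a latent-normal count; baseline-to-month-6 correlation 0.60–0.75; mean worsening 0.3 SD in the manual arm; benefit 0.28 residual SD; 12%, 20% or 30% with 3 or more criteria. In a proportional-odds model adjusted for baseline, power is 0.54–0.62 on categories and 0.65–0.73 on the count, a loss of 10–14 points. With 400–500 trials per scenario, the Monte Carlo standard error of one power estimate is at most √(0.25/400) = 0.025.

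*Simulation B.* Inputs: 198 survivors per arm (215 × 0.92 = 197.8); 30–50% worsening in the manual arm and about one third fewer in the automated arm; 10–20% improving; one fifth of changes being two steps. Month-6 value regressed on baseline value and arm:

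| Assumed mix | Points lost over five change scenarios |
|---|---|
| 50/40/10 | 6–13 |
| 40/47/13 | 10–18 |
| 25/50/25 | 14–23 |
| 15/45/40 | 17–31 |

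For example, at 40/47/13 with 40% against 27% worsening and 10% improving, power is 0.61 on the count and 0.45 on categories: 16 points. Other test choices in simulation B gave 12–32 points (mean change) and 18–43 points (any worsening, yes or no). The categories lost power in every scenario.

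**The case against.** The strongest reply is that three-level status is a recognised classification and answers a question the trial asks: the Background hypothesizes fewer occurrences of frailty, which is a category transition. That stands, and it is a reason to keep the transition table. It does not remove the ceiling for patients already frail.

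A second reply is that the size of the loss comes from the chosen assumptions. That also stands. The article's general-population figures for frailty run from 4% to 26% by age, so the mixes with 30% or 40% frail lie above anything it cites. Without the 15/45/40 mix, simulation B's adjusted loss is 6–23 points. Both simulations spread the effect over the whole scale, which favours the finer measure.

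Third, the telephone proxies for grip and gait can create spurious one-point changes, to which the count is more exposed. Neither simulation includes this error, so the gain may be smaller than shown.

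Fourth, the consequence is limited. This is a secondary outcome with no stated power. Death and loss of autonomy in frail patients enter the primary outcome, and ADL, IADL, the Edmonton criteria and the Timed Up and Go test are also collected. The Discussion's recommendation is conditional.

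A reader might infer that a fixed third of changes is lost, or that the cut costs up to about 25 points in this trial. The article supports neither. About a third fits only a mostly robust sample. In simulation A, gaps of 21–24 points appear only when an unadjusted test on categories (0.44–0.49) is set against an adjusted model on the count (0.65–0.73), which credits the cut with the gain from adjustment. The article fixes no test for this outcome.

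**Conclusion.** The point holds as a weakness of sensitivity and ceiling in a secondary outcome, not as an error. Two parts are certain: patients frail at baseline cannot be recorded as worsening, and changes within a category are not seen. The size is conditional: roughly 28–54% of count changes invisible and about 6–31 points of power lost with a baseline-adjusted model, under assumed case mixes and change rates and with frail taken as 3 or more. Deaths and telephone-proxy error are outside these figures.

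A reader might go further and conclude that a finding of similar frailty status would be an artefact, or that the trial's power is compromised. The first is too strong: the scale contributes to apparent stability, but moves across the boundaries are still recorded. The second is wrong, because the 430 patients rest on the primary outcome alone. This is a cheap improvement worth making.

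**What to change.** In Statistical analysis, define the frailty outcome as the number of Fried criteria (0–5) at month 6, compared between arms with a proportional-odds model adjusted for baseline count and surgical risk. In addition:

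- Give deaths an explicit place, for example as the worst level, in line with the primary outcome.
- Add a sensitivity analysis that excludes or flags month-6 assessments made by telephone.
- Keep the robust / pre-frail / frail transition table as a descriptive display, and leave the stratification unchanged.
- Reconcile the cut-points in Frailty status, where a count of exactly 3 belongs to no category. The table and the stratification depend on this whichever outcome is used.

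The cost is a few sentences, one ordinal model and one sensitivity analysis, with no extra patients or procedures. There are two small downsides: an odds ratio on the count is less familiar to clinicians than a category shift, and the count is more exposed to one-point noise from the telephone proxies.
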